#### Durability of the 24-week intervention

This will be assessed using the repeatedly-measured outcomes collected quarterly for 12 months following end of the trial intervention, following the theoretical and simulation approaches and results provided by Lu et al. (2016) [198] and Li (2017) [199]. These data will be modeled using marginal means models with generalized estimating equations, with weighting and replication of observations based on stage 1 responder status, as recommended for SMART designs. Using this approach, the post-intervention linear slopes as well as end-of-study absolute values in trial outcomes will be compared among the adaptive treatment strategies (assessing group-by-time interaction terms); we will also consider possible non-linearities in post-intervention trajectories with addition of polynomial terms for time of assessment. Adverse events will be categorized using the MedDRA coding system and compared between treatment groups using exact methods for comparisons of proportions.

#### Multiplicity

The primary outcome (Youth SCARED) will be tested at an α = 0.05. Evaluation of secondary, exploratory, and all subgroup analyses will control for the false discovery rate [200].

### Sensitivity analyses

These will assess the impact of analytic and modelling assumptions related to selection of covariates, handling of missing data, and adherence to randomized intervention. They will compare parameter estimates and statistical conclusions of treatment group differences on outcomes to study the differential impacts of various assumptions, and will include: (1) additional baseline covariates that differ between groups, evidenced by a standardized difference ≥ 0.1; (2) trial dropouts in the 24-week analysis, using multiple imputations to attain 20 complete trial datasets and summarizing treatment effects over the repeatedly imputed datasets; (3) an adherence-based analysis, limiting analyses to subjects who participated in ≥80% of planned intervention contacts and took ≥80% of medication doses based on pill counts..

#### Effects of treatment modality

We will evaluate the association of percentage telehealth sessions with session attendance and completion of the trial. We will also assess the influence of telehealth delivery variables (whether sessions were conducted in person or via telehealth, whether the patient’s video platform was a computer or a smartphone, and whether any technical difficulties in implementation were encountered) on treatment outcomes by including them as covariates in our sensitivity analyses.

### Statistical methods to address missing data

Trial dropouts will be reported by follow-up visit and summarized by reason for dropout. Missing data for trial outcomes will be analyzed to provide insight on the missing data mechanism. We will inspect patterns of missing data by each randomized group. Baseline characteristics will be compared between participants with and without complete outcome data. Participant characteristics found to be related to missingness will be correlated with values of the outcome variable (baseline values and among participants who have complete data); we will evaluate the relationship of baseline values of the outcome variable to missingness at each follow-up. Following the recommendation of Shortreed et al. (2014) [201], we will employ conditional imputation models for missing data that take advantage of the time- and stage-ordered nature of the trial design. At each time point, missing data (outcomes and covariates) will be imputed using baseline, outcome measures, randomized treatments, and remission indicators measured prior to the time of the missing data collection. For participants who are lost to follow-up prior to the Stage 2 randomization, we will perform a single imputation, assigning a status of non-remitter (i.e., non-responder) at 12 weeks. Multiply imputed datasets will then include an imputation for the missing Stage 2 randomization and imputations of subsequent outcomes. We will document and appropriately follow participants depending on their type of dropout (e.g., dropout from study only but maintaining physician/site service, vs dropout from study and service). Dropouts and reasons will be summarized in the final trial CONSORT diagram. Sensitivity analyses will compare results (treatment means, treatment group differences, and statistical conclusions regarding group differences) from models with only complete cases with results from models incorporating missing data through multiple imputation.

### Heterogeneity of treatment effects (HTE)

Our study data will include a rich body of information on *tailoring variables*, including baseline individual, family, and context characteristics, some related directly to child anxiety and its clinical portrait: past treatment response, family history of anxiety, SES, and variables that are *potentially modifiable*, such as overall symptom severity [29, 31], functional impairment [29, 31], severity of depression and other comorbid illnesses, treatment fidelity and adherence, medication dose, treatment setting (community or university; primary pediatric or specialty mental health clinic), and parental depression [111] or anxiety [112, 202]. These tailoring variables, used in post-hoc analyses, will help shed light on how patterns of response through the various pathways of this SMART study may relate to individual, family, or context characteristics at the beginning of treatment. One important product from this trial will be the development of a prospective, adaptive intervention algorithm – a set of tailored clinical pathways based on (a) participant characteristics at baseline and (b) response to intervention after acute intervention. This adaptive treatment algorithm will have immediate clinical applicability in populations of diverse and vulnerable youth.

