
#### Contextualizing factors

Also termed patient “tailoring variables”, these factors modify treatment response. Candidates for tailoring variables include baseline individual, family, and context characteristics, some of which relate directly to child anxiety and its clinical portrait: ethnicity [30], SES [32], past treatment response [29, 31], and family history of anxiety; and variables that are potentially modifiable, such as overall symptom severity [29, 31], functional impairment [29, 31], the nature and severity of comorbid illnesses, treatment fidelity and adherence, and treatment setting (community or university; primary pediatric or specialty mental health clinic).

We theorize that demographic characteristics such as ethnicity [30] and SES [32] will function as *cultural factors* that will influence the nonspecific factors of therapeutic alliance, clinician relatedness, and treatment adherence. Data from the CAMS trial support these hypotheses. In CAMS, African-American youths attended fewer CBT and medication management sessions, and they were rated by therapists as less involved and compliant with treatment and, possibly as a consequence, as showing a lower level of mastery of CBT concepts [41]. Controlling for these process factors and SES eliminated racial differences in outcome. Similarly, patient nonadherence (poor attendance, low homework completion, poor compliance in session) was associated with number of parents present in the home (with the best outcomes for two-parent families), although indices of nonadherence varied in their power to predict clinical outcomes [124]. In contrast, we expect the modifying effects of *illness-related factors*, such as depression and other comorbid illnesses, baseline anxiety severity, and family history of anxiety, will operate through their impact on the *Coping Cat*-specific factors, exposure and development of coping skills [29, 31, 119]. Table 2 specifies how we will measure each of these contextualizing constructs.

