##### Maintaining treatment assignment

Clinicians and participants will be coached at study entry that adherence to the study treatment assignment is essential, as a relatively small proportion of crossovers can be detrimental to the trial. Medication adherence will be assessed with pill counts at each clinic visit.

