#### HTE analysis plan

Dividing the total sample into pre-defined subgroups, we will use analytic methods detailed above to estimate treatment effects across subgroups. Forest plots of mean treatment group differences with confidence intervals for each subgroup will be completed to graphically evaluate uniformity of treatment effect. In the total sample, we will first add the subgroup as a main effect covariate. Evaluation of the subgroup main effect will test over the entire sample (combined intervention groups) whether and to what extent outcomes in general differs by SES, ethnicity, comorbid depression, social anxiety disorder, and treatment setting.

We will employ Q-learning as our primary approach to testing the heterogeneity of treatment effects. This is a regression approach recommended for SMART data to identify tailoring variables that modify treatment responses and suggest enhancements to the sequential decision-making of an adaptive intervention [197]. In this 2-stage SMART design with a continuous trial outcome, Q-learning with linear regression will be used in 2 steps. In step 1, the Stage 2 decision rule will be optimized among Stage 1 non-remitters, identifying individual variables that significantly modify the Stage 2 randomization effect. In step 2, the Stage 1 decision rule will be optimized, controlling for the optimized Stage 2 intervention and identifying individual variables that significantly modify the Stage 1 randomization effect. This approach therefore may suggest a more tailored adaptive intervention that could be evaluated in a future SMART study.

As there will remain clinical subgroups of primary interest to clinicians, we will also assess in a secondary analysis the randomized treatment-by-subgroup (e.g., treatment-by-SES group) interaction terms to estimate and test for differences in treatment effects (Main Effects 1 & 2) by subgroup. Estimating treatment effects across our carefully pre-defined subgroups, we will use forest plots of mean treatment group differences with confidence intervals for each subgroup to show subgroup-specific effects and graphically evaluate uniformity of treatment effects.

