With an estimated 20% dropout, we will be able to detect the following effect sizes for Main Effect 1 (total *n* = 324) in various subgroups by sample representation (n): (1) Effect Size = 0.40 for 60% representation (*n* = 194); (2) Effect Size = 0.44 for 50% representation (*n* = 162); (3) Effect Size = 0.50 for 40% representation (*n* = 130). For Main Effect 2 (total n = 194), we will be able to detect: (1) Effect Size = 0.52 for 60% representation (*n* = 116); (2) Effect Size = 0.58 for 50% representation (*n* = 96); (3) Effect Size = 0.64 for 40% representation (*n* = 78). Subgroup interactions will be tested formally; with the total anticipated sample size of 324 to complete the 24-week intervention, we will have 80% power to detect subgroup differences in treatment effect sizes of ~ 0.65 and higher for Main Effect 1, and ~ 0.8 and higher for Main Effect 2.

In additional exploratory analyses, we will use latent class/profile analysis to model heterogeneity of outcome response patterns, assuming categorical latent variables (latent groups) for response. Latent class/profile analysis has been proposed as an alternative to subgroup analysis in clinical trials. As an exploratory analysis, it uses observed data (e.g., clinical characteristics, randomized treatments) to identify latent group classifications that may suggest individual characteristics related to greater responses to treatment [205].

In addition to assessing the effects of telehealth delivery of treatment on outcomes, we will assess whether the percentage of treatment sessions conducted via telehealth moderates treatment outcomes. This test will tell us whether discontinuities in telemedicine use over the course of the study or within individual patients has influenced our findings. We will also assess whether session attendance and trial completion differ by degree of participation in telehealth vs in-person intervention.

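### Adherence, fidelity, medication dose and telehealth share arise after Stage 1 randomization but are to be tested as tailoring variables or moderators with no rule on when they are measured

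*Protocol article*

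**What the plan says.** The Contextualizing factors section, which treats these factors as modifiers of treatment response, includes "the nature and severity of comorbid illnesses, treatment fidelity and adherence, and treatment setting". The section Heterogeneity of treatment effects (HTE) repeats the list and adds dose: "treatment fidelity and adherence, medication dose, treatment setting". The Mediation analyses section then commits to testing moderator effects of the contextualizing factors under the HTE plan.

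The HTE section says the tailoring variables show how response "may relate to individual, family, or context characteristics at the beginning of treatment". It describes the resulting algorithm as "a set of tailored clinical pathways based on (a) participant characteristics at baseline and (b) response to intervention after acute intervention".

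The HTE analysis plan makes Q-learning the primary method. Its second step concerns the Stage 1 rule and consists of "identifying individual variables that significantly modify the Stage 1 randomization effect". The same section adds: "we will assess whether the percentage of treatment sessions conducted via telehealth moderates treatment outcomes". Under Effects of treatment modality, telehealth use, video platform and technical difficulties are examined "by including them as covariates in our sensitivity analyses".

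On timing, Maintaining treatment assignment states: "Medication adherence will be assessed with pill counts at each clinic visit". Under Process evaluation, medication fidelity is sessions attended plus pill counts, and CBT fidelity is attendance plus achievement of the core functions. The Stage 1 dosing text ties dose increases to non-remission and tolerability. Telehealth is recorded session by session.

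**The concern.** Randomization makes the arms comparable on everything fixed before it. It does not do so for what happens afterwards. If a variable formed during treatment is crossed with the randomized arm, the interaction coefficient mixes true effect modification with any difference between arms in how that variable tracks prognosis.

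The protocol gives reasons to expect such a difference. Adherence and fidelity are measured differently in the two arms. The Aim 1 hypotheses cite poorer CBT adherence among ethnic minorities, who will be strongly represented here. Dose follows response. Several sites had long delivered pharmacotherapy wholly by telehealth, while psychotherapy by telehealth was still growing, so telehealth share may depend on arm.

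What is at stake is the tailoring output, which the protocol presents as an important product ready for clinical use. Adherence or dose could be reported as modifying the choice between CBT and fluoxetine when it only marks children who were going to do better or worse. A clinician choosing a first treatment knows neither.

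**Working it through.** **1. Timing of each variable.**

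| Variable | When it arises | Usable for the Stage 1 rule? | Usable for the Stage 2 rule? |
|---|---|---|---|
| SES, ethnicity, comorbid depression, social anxiety, setting | Before Stage 1 randomization | Yes | Yes |
| Adherence and fidelity, weeks 0–12 | After Stage 1, before Stage 2 randomization | No | Yes |
| Dose, weeks 0–12 | As above, medication-first only | No, undefined for CBT-first | Yes, within medication-first |
| Telehealth share, weeks 0–12 | After Stage 1, before Stage 2 randomization | No | Yes |
| Any of these, weeks 12–24 | After Stage 2 randomization | No | No |

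The HTE text draws no such line, and its phrase about the beginning of treatment does not fit adherence, fidelity or dose.

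**2. The plan's own figures.** No figure is in dispute; they supply the sample sizes. With 1.960 + 0.842 = 2.802, the detectable Main Effect 1 at 324 completers is 2.802 × 2/√324 = 0.311 (stated 0.31). The detectable subgroup interaction is 2.802 × √(4/(fN) + 4/((1−f)N)), where f is the subgroup share. For f from 0.5 to 0.3 this gives 0.62 to 0.68 at N = 324 (stated about 0.65) and 0.81 to 0.88 at N = 194 (stated about 0.8).

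**3. False-interaction rate.** Assumptions, none of them in the protocol: outcome SD 1 within arm; a constant treatment effect, so no true effect modification; unmeasured prognosis with coefficient 0.5; a standardized post-randomization variable correlated r with prognosis in one arm and 0 in the other; one unadjusted two-sided 0.05 test of arm × variable.

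- Slope difference δ = 0.5 × r.
- SE ≈ √(1/n + 1/n) for n per arm: √(2/162) = 0.111, and √(2/97) = 0.144.
- Rejection rate ≈ Φ(δ/SE − 1.96) + Φ(−δ/SE − 1.96).

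| r | δ | δ/SE, N = 324 | Formula | Simulated | δ/SE, N = 194 | Formula | Simulated |
|---|---|---|---|---|---|---|---|
| 0.2 | 0.10 | 0.90 | 15% | 15% | 0.70 | 11% | 10% |
| 0.4 | 0.20 | 1.80 | 44% | 43% | 1.39 | 28% | 27% |
| 0.6 | 0.30 | 2.70 | 77% | 78% | 2.09 | 55% | 56% |

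The simulations used 4,000 trials per row and ordinary regression, not the full Q-learning procedure.

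**4. Controls.** With r = 0.4 in both arms, the simulated rate at N = 324 is 5.1%. With a baseline variable in place of the post-randomization one, it is 4.9% to 5.8%. The inflation therefore needs a relation to prognosis that differs by arm.

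**The case against.** The case on the other side has weight.

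- A reader might infer that listing adherence, fidelity and dose as tailoring variables is an error in itself. It is not. In a two-stage SMART, their Stage 1 values precede the Stage 2 randomization and may validly tailor the second decision.
- A reader might infer that the final algorithm will use them to choose the first treatment. The text does not say so: the stated inputs are baseline characteristics and acute response. The subgroups named in the HTE plan are baseline variables, the wider list is called post hoc, and Q-learning is meant to suggest a rule for a future trial.
- A reader might infer that telehealth share is simply a consequence of assigned treatment. The protocol attributes it largely to site practice and the pandemic, and dependence on arm is only plausible. The telehealth covariates enter sensitivity analyses only.
- A correlation of 0.2 with the outcome itself would give 44%, and 0.3 would give 78%. That is the same δ on another scale (0.5 × 0.4 = 0.2; 0.5 × 0.6 = 0.3). Smaller correlations with an imperfect prognostic factor do much less.
- Exploratory and subgroup tests are under false-discovery-rate control, so the rates above are not those of the planned procedure. That control limits chance findings; it does not remove bias.
- The candidates for each Q-learning step could sit in an analysis plan that is not shown. Their absence alone would be no finding.

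What remains is in the article itself: it lists these variables, commits to testing moderator effects of the contextualizing factors and of telehealth share, and describes tailoring variables in terms that exclude them.

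**Conclusion.** The point holds as an internal conflict with a methodological consequence. For Main Effect 1, adherence, fidelity, dose and telehealth share observed during treatment cannot inform a starting rule and can produce false effect modification. The same bias applies to Stage 2 values used for Main Effect 2. Dose has no meaning as a modifier of the Stage 1 contrast.

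The size is conditional: about 15% to 78% false interactions at 162 per arm under the assumed correlations, 10% to 56% at 97 per arm, and the nominal 5% when the relation to prognosis is equal in both arms. The protocol gives no correlations, so these figures illustrate a range and do not predict a rate. The primary treatment contrasts do not use these variables and are unaffected.

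**What to change.** In the HTE section and the HTE analysis plan, state that:

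- tailoring variables and moderators for Stage 1 (Main Effect 1) are limited to those measured before Stage 1 randomization;
- those for Stage 2 (Main Effect 2) are limited to those measured by week 12, before Stage 2 randomization. Stage 1 adherence, fidelity and telehealth share are then allowed, and Stage 1 dose within medication-first children only;
- associations with concurrent adherence, fidelity, dose and telehealth are descriptive and non-causal. This includes the telehealth covariate models under Effects of treatment modality and the telehealth percentage test.

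If a telehealth moderator of Main Effect 1 is wanted, build it from pre-randomization information such as site and enrolment date. The protocol does not record each site's telehealth status by date, so the plan should not rely on that.

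The change is a few sentences, with no effect on sample size, visits or instruments. The cost is that concurrent adherence, dose and telehealth are described, not tested as moderators; changes in telehealth use within a child, which the current test is meant to address, would also be covered only descriptively.

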#### HTE analysis goals: pre-specified hypotheses and supporting evidence base

Based on findings from prior studies, we hypothesize that predictors of poor acute treatment outcomes will include lower SES [31, 32], ethnic minority status [30, 41], comorbid depression [203], a diagnosis of social anxiety disorder [28, 31, 32, 204], and treatment in a pediatric rather than a specialty mental health clinic [31]. More severe anxiety will predict better response to Stage 2 combined CBT + fluoxetine treatment than either treatment modality alone [49, 50].

#### HTE analysis plan

Dividing the total sample into pre-defined subgroups, we will use analytic methods detailed above to estimate treatment effects across subgroups. Forest plots of mean treatment group differences with confidence intervals for each subgroup will be completed to graphically evaluate uniformity of treatment effect. In the total sample, we will first add the subgroup as a main effect covariate. Evaluation of the subgroup main effect will test over the entire sample (combined intervention groups) whether and to what extent outcomes in general differs by SES, ethnicity, comorbid depression, social anxiety disorder, and treatment setting.

We will employ Q-learning as our primary approach to testing the heterogeneity of treatment effects. This is a regression approach recommended for SMART data to identify tailoring variables that modify treatment responses and suggest enhancements to the sequential decision-making of an adaptive intervention [197]. In this 2-stage SMART design with a continuous trial outcome, Q-learning with linear regression will be used in 2 steps. In step 1, the Stage 2 decision rule will be optimized among Stage 1 non-remitters, identifying individual variables that significantly modify the Stage 2 randomization effect. In step 2, the Stage 1 decision rule will be optimized, controlling for the optimized Stage 2 intervention and identifying individual variables that significantly modify the Stage 1 randomization effect. This approach therefore may suggest a more tailored adaptive intervention that could be evaluated in a future SMART study.

As there will remain clinical subgroups of primary interest to clinicians, we will also assess in a secondary analysis the randomized treatment-by-subgroup (e.g., treatment-by-SES group) interaction terms to estimate and test for differences in treatment effects (Main Effects 1 & 2) by subgroup. Estimating treatment effects across our carefully pre-defined subgroups, we will use forest plots of mean treatment group differences with confidence intervals for each subgroup to show subgroup-specific effects and graphically evaluate uniformity of treatment effects.

With an estimated 20% dropout, we will be able to detect the following effect sizes for Main Effect 1 (total *n* = 324) in various subgroups by sample representation (n): (1) Effect Size = 0.40 for 60% representation (*n* = 194); (2) Effect Size = 0.44 for 50% representation (*n* = 162); (3) Effect Size = 0.50 for 40% representation (*n* = 130). For Main Effect 2 (total n = 194), we will be able to detect: (1) Effect Size = 0.52 for 60% representation (*n* = 116); (2) Effect Size = 0.58 for 50% representation (*n* = 96); (3) Effect Size = 0.64 for 40% representation (*n* = 78). Subgroup interactions will be tested formally; with the total anticipated sample size of 324 to complete the 24-week intervention, we will have 80% power to detect subgroup differences in treatment effect sizes of ~ 0.65 and higher for Main Effect 1, and ~ 0.8 and higher for Main Effect 2.

In additional exploratory analyses, we will use latent class/profile analysis to model heterogeneity of outcome response patterns, assuming categorical latent variables (latent groups) for response. Latent class/profile analysis has been proposed as an alternative to subgroup analysis in clinical trials. As an exploratory analysis, it uses observed data (e.g., clinical characteristics, randomized treatments) to identify latent group classifications that may suggest individual characteristics related to greater responses to treatment [205].

In addition to assessing the effects of telehealth delivery of treatment on outcomes, we will assess whether the percentage of treatment sessions conducted via telehealth moderates treatment outcomes. This test will tell us whether discontinuities in telemedicine use over the course of the study or within individual patients has influenced our findings. We will also assess whether session attendance and trial completion differ by degree of participation in telehealth vs in-person intervention.

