##### Parent-completed background materials

The *Patient/Subject Profile* is a systematic review of participants’ medical, psychiatric, and treatment history, as well as family history of psychiatric illnesses. SES will be quantified using the Hollingshead Index of Social Status [159], augmented with more contemporary measures of material hardship and perceived social status [160–162].

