(3) Group main effect ESs were then computed for a Stage 1 remission rate of 40%. Our estimated Stage 1 remission rate of 40% is a conservative estimate based on the CAMS remission rate of 35% achieved for ethnic minorities, when applying remission criteria less stringent than ours [30]. In CAMS, the 12-week remission rate was also approximately 10% higher in medication-only compared to CBT-only. We used this 10% difference in these calculations to compute ESs and resulting sample size estimates. For Main Effect 1 (start with medication vs start with CBT), ESs for all 3 medication or CBT groups (1: remitter; 2: non-remitter➔optimize monotherapy; 3: non-remitter➔medication+CBT) were computed as a weighted average of the group-specific ESs. Weights were the remission rate, with the non-remitter weight (1 minus remission-rate) split equally among the 2 randomized non-remitter groups (reflecting 1:1 Stage 2 randomization among non-remitters). For Main Effect 2 (among Stage 1 non-remitters, optimize Stage 1 treatment vs add the other treatment), ESs were computed as a weighted average of the ESs for monotherapy optimizers (medication+, CBT+) and a weighted average of the combined (medication+CBT, CBT + medication) groups. These weights were again 0.5*(1- remission-rate).

[4] We then computed the sample size required to detect Main Effect 2 (optimize monotherapy vs add the other therapy in non-remitters) at 80% power and tested at a 2-sided alpha = 0.05. From our computations above, the Main Effect 2 ES was approximately 0.40 SD, requiring a sample size of 194 participants among Stage 1 non-remitters. Increasing the sample size of 194 by the non-remission rate (N divided by non-remission rate) and by the estimated 20% dropout rate, yielded a sample size of 404 (202 per group) for Stage 1 remission rates of 40%. Randomizing 404 participants, with an estimated 324 finishing the trial and a remission rate of 40%, will provide the ability to detect an overall Main Effect 1 (medication first versus CBT first) ES of ≥0.31 SD with 80% power.

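### The secondary treatment-by-SES interaction tests use groups although SES is measured on a graded index, giving up power in tests the plan already shows to be weak

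*Protocol article*

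**What the plan says.** The HTE analysis plan in the protocol article describes two routes to effect modification. The main one is Q-learning with linear regression, run in two steps that mirror the two randomizations; nothing there says that modifiers are categorised. The second is a subgroup analysis: "Dividing the total sample into pre-defined subgroups, we will use analytic methods detailed above to estimate treatment effects across subgroups". Forest plots show the subgroup effects, and a secondary analysis tests "randomized treatment-by-subgroup (e.g., treatment-by-SES group) interaction terms" for Main Effects 1 and 2. The factors listed for the subgroup work are SES, ethnicity, comorbid depression, social anxiety disorder and treatment setting. No cut-points or numbers of groups are given.

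On measurement, the section on parent-completed background materials says "SES will be quantified using the Hollingshead Index of Social Status", supplemented by measures of material hardship and perceived status.

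On power, the HTE analysis plan says "we will have 80% power to detect subgroup differences in treatment effect sizes of ~ 0.65 and higher for Main Effect 1". The matching threshold for the Stage 2 comparison is about 0.8 SD. Its within-subgroup figures are for groups holding 60%, 50% and 40% of the sample. The Multiplicity section adds: "Evaluation of secondary, exploratory, and all subgroup analyses will control for the false discovery rate".

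The section on reporting pre-specified analyses commits the primary outcome paper to forest plots for all subgroups and to tests of treatment-subgroup interactions. It does not mention Q-learning.

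**The concern.** SES is recorded on a graded scale, yet the interaction test that the protocol gives as its example uses SES groups. Grouping treats everyone within a group as alike and so discards information already collected. Interaction tests can least afford this: the detectable differences of about 0.65 and 0.8 SD compare with detectable main effects of 0.31 and 0.40 SD in the sample size section. At stake is power. A real SES gradient in treatment effect is more likely to be missed, and the primary paper is then more likely to report no evidence of modification in a trial aimed at underserved families. Main Effects 1 and 2 are untouched, and no bias is alleged.

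**Working it through.** **Inputs.** Completers: 324 for Main Effect 1 and 194 non-remitters for Main Effect 2 (sample size section and HTE analysis plan). Allocation is 1:1 at both stages (Randomization). Error rates: "at 80% power and tested at a 2-sided alpha = 0.05", stated for the Main Effect 2 sample size and assumed here to carry over to the interaction figures. Outcome SD = 1. Then z(0.975) + z(0.80) = 1.960 + 0.842 = 2.802.

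**Step 1: reproduce the plan's interaction figures.** With a share p of N participants in one of two subgroups, the smallest detectable difference between the subgroup effects is 2.802 × √(4/(Np) + 4/(N(1−p))).

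- Main Effect 1, N = 324: 50/50 gives 2.802 × √(8/162) = 0.623; 60/40 gives 0.635. Stated: about 0.65.
- Main Effect 2, N = 194: 50/50 gives 2.802 × √(8/97) = 0.805; 60/40 gives 0.821. Stated: about 0.8.

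The stated figures therefore agree, after rounding, with two-group contrasts split near the middle. Against the main effects, 0.65/0.31 = 2.1 and 0.8/0.40 = 2.0.

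**Step 2: information kept by a two-group split.** For a normal score cut at the point c that puts a share p in one group, with treatment modification linear in the score, the share kept is φ(c)²/(p(1−p)), where φ is the standard normal density.

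- 50/50: 0.3989²/0.25 = 0.637, a loss of 36%
- 60/40: 0.622, a loss of 38%
- 70/30: 0.576, a loss of 42%
- 80/20: 0.490, a loss of 51%

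At the median, N = 324 acts like 324 × 0.637 = 206, and N = 194 like 124.

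**Step 3: what that means for power.** At the median the correlation between split and score is √0.637 = 0.798.

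- A modifier with 80% power when split has, as a score, Φ(2.802/0.798 − 1.960) = Φ(1.55) = 94%.
- A modifier with 80% power as a score has, when split, Φ(2.802 × 0.798 − 1.960) = Φ(0.28) = 61%.
- On the median-split scale, the detectable difference moves from 0.623 to 0.623 × 0.798 = 0.50 SD (Main Effect 1) and from 0.805 to 0.64 SD (Main Effect 2).

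A simulation of 4,000 trials at each size, with a normal modifier and a linear gradient, gave power of 93% (score) against 78% (median split) at N = 324, and 92% against 79% at N = 194.

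**Step 4: other assumptions.** The protocol gives neither cut-points nor the SES distribution, so the loss is a range.

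- Tertiles of a normal score, scored linearly: 79.3% kept, a loss of 21%. Power of 80% when grouped becomes Φ(2.802/√0.793 − 1.960) = 88% as a score.
- Uniform score split at the median: 75% kept, a loss of 25%; 80% becomes 90%.
- Strongly skewed (exponential) score split at the median: 48% kept, a loss of 52%; 80% becomes 98%.

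If the plan's 80% figures assume a two-sided 0.05 level, false discovery rate control would lower the power of these tests further.

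**The case against.** The strongest reply is that the main test of heterogeneity is not a split at all. Q-learning with linear regression can take scores, and the subgroup interactions are secondary, included because clinicians will want to see particular subgroups. That stands. A reader might infer that the plan tests all effect modification by dividing the sample; the protocol does not support that.

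A reader might also infer that depression and anxiety severity will be cut. The documents do not show this. Comorbid depression may enter as a diagnosis; its severity appears only among the tailoring variables. The severity hypothesis, "More severe anxiety will predict better response to Stage 2 combined CBT + fluoxetine treatment than either treatment modality alone", has no stated form, and anxiety severity is not among the listed subgroup factors. The first Q-learning step, on modifiers of the Stage 2 randomization, could address it. The cut at 33 on the SCARED-41 is a randomization stratum. Nor is there a general policy of categorising: the percentage of telehealth sessions is to be examined as a moderator. Only SES is documented as grouped.

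Normality and linearity are also unproven. The sample is predominantly underserved, so SES may be skewed, and a threshold effect near the cut could favour a split.

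Finally, coding of moderators is often left to an analysis plan, which is not shown. That would answer a complaint about missing cut-points. It does not answer this one, because the protocol itself names the grouped form, gives power for subgroup contrasts and promises those tests in the primary paper.

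**Conclusion.** The point holds in a narrow form: in the secondary interaction tests promised for the primary paper, SES is tested as groups although a graded measure is available, and those tests are already weak by the plan's own figures. With two groups split near the middle, a roughly normal score and a linear gradient, about 36% of the information is lost, which is the difference between 80% and about 94% power. A flat claim that a third or more is always lost would go too far: it is 21% for tertiles and 25% for a uniform score, while uneven splits or strong skew lose more. The protocol's power figures are not wrong; they reproduce. This is a worthwhile improvement to a secondary analysis and does not threaten the trial's main conclusions.

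**What to change.** Test the Stage 1 and Stage 2 treatment-by-SES interactions with SES as a continuous score, and add a nonlinearity check such as a spline term. Do the same for depression and baseline anxiety if they would otherwise be cut from scores. State that Q-learning uses the same continuous scores. Keep the cut subgroups for forest-plot display, so that clinicians still see the subgroup estimates. Ethnicity, social anxiety disorder and treatment setting stay categorical.

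The cost is a few lines of analysis-plan wording, with no extra participants or measurements. The downside is that the main interaction test then assumes a roughly linear gradient, which the nonlinearity check addresses.
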